#### Procedure

Practitioners at each site will ask families with children who meet inclusion criteria if they consent to participate. Each site will administer index and reference tests as clinically appropriate. Index tests will be administered by trained practitioners including Aboriginal Health Workers, nurses, midwives, allied health, General Practitioners (GPs) and/or paediatricians (when available). Reference tests will be administered by allied health clinicians with relevant qualifications and credentialing for the tool (e.g., psychologists, occupational therapists, speech therapists), who have training and experience diagnosing FASD, consistent with the Australian guide to the diagnosis of FASD.^5^ Where possible, index tests and reference tests will be administered by different practitioners. Practitioners administering index tests will not have access to reference test results, and vice versa, until all tests are scored. When index or reference tests have been completed by third parties (e.g., the school), families will be asked for their consent to share data with participating study sites. A member of the research team will audit health records to extract test scores from completed assessments.

All practitioners and the research team will receive training in study protocols to ensure fidelity prior to administering tests and extracting data. Training will include: purpose of the project, rationale for test selection and use of the RNDA. RNDA training includes studying standardised training videos developed by certified RNDA trainers, scoring training tapes, video recording assessments with a sample child and a review of this video by a certified scorer (to ensure fidelity). If a site does not have practitioners available to complete a test, clinicians with relevant qualifications from the research team will administer the missing test. Check-in meetings with practitioners at each site will be held quarterly to ensure continued fidelity with study protocols. All index and reference tests aim to be completed within 9 months of the administration of the first test.

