## Abstract

**Introduction:**

Australian practices for diagnosing fetal alcohol spectrum disorder (FASD) are lengthy and require specialist expertise. Specialist teams are based in urban locations; they are expensive and have prolonged waitlists. Innovative, flexible solutions are needed to ensure First Nations children living in rural/remote communities have culturally appropriate and equitable access to timely diagnosis and support. This study compares the accuracy of rapid assessments (index tests) that can be administered by a range of primary healthcare practitioners to specialist standardised FASD assessments (reference tests). The cost-efficiency of index tests will be compared with reference tests.

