## Introduction

Fetal alcohol spectrum disorder (FASD) affects between 1 - 5% of Australian children, and up to 19% in some remote Australian communities, which is higher than any other neurodevelopmental disorder.^1–4^ To identify FASD, current Australian guidelines recommend comprehensive diagnostic assessments (reference tests) across 10 neurodevelopmental domains, delivered by multidisciplinary teams. These assessments are primarily available in Australia at specialist services, making this a lengthier and more costly diagnostic process than any other neurodevelopmental disorder.^5^ Current waitlists for Australian children suspected of FASD are up to 3 years at some health services. Overall, specialist services are only seeing a small proportion of suspected cases and children from rural and remote regions are left behind.^6 7^

To meet the demand for diagnosis, our Australian health system either needs an inordinate number of specialists and multidisciplinary clinics, or we need to think differently about how to diagnose FASD. Our health system is unlikely to be able to resource the longest, most costly assessment process for one of the most prevalent neurodevelopmental disorders in children, but the use of valid and reliable rapid assessment tools could leverage capacity within primary care, increasing vulnerable children’s access to diagnosis.

In this project we will conduct a two-phase study to: (1) determine the diagnostic accuracy of rapid neurodevelopment assessments (index tests) that can be used to detect FASD in primary healthcare (Phase I)^8^; and (2) examine the economic benefits of leveraging primary healthcare to support specialist practitioners in the diagnosis of FASD, in terms of cost for families and healthcare systems (Phase II).

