##### Clinical assessment information

*Child developmental history* will be obtained from caregiver interviews and will include: gestational age at birth, prenatal exposures (e.g., prescription medication, illicit drug use), birth complications, family and child medical and mental health history, children’s adverse life events, and parent reports of children’s learning, speech, behavioural and emotional difficulties. Where possible, *maternal alcohol consumption in pregnancy* will be assessed using the three-item Alcohol Use Disorders Identification Test-Concise (AUDIT-C).^10^ Each item is scored from 0 to 4, with higher scores indicating increased alcohol usage. Total scores range from 0 (no alcohol consumption) to 12; a score of 3 or above for women indicates hazardous drinking. The AUDIT-C has convergent validity with the 10-item version of the scale.^11^
*Sentinel features,* including the standard frontal, three-quarter and lateral facial photographs will be collected and analysed using the Fetal Alcohol Spectrum Facial Photographic Analysis Software V.2.0.^12^

*Index tests* were selected by clinical specialists with expertise in FASD, subsequently approved by site practitioners and the project steering committee. Table 1 outlines the rationale for index test selection.

**Table 1 T1:** Rationale for selection of index tests

Rapid Neurodevelopmental Assessment^13^	Behaviour Assessment System for Children Third Edition^18^
Delivered by non-specialists trained to certification in administration, important for rural and remote sites lacking specialists.	Established reliability and validity within the Australian context^25^
Developed for use in low social-economic status populations,^26 27^ important for rural and remote Australians where 13.3% of the population live below the poverty line.^28^	Covers a broad array of neurodevelopmental domains, including executive and adaptive function, key fetal alcohol spectrum disorder diagnostic domains not commonly assessed in other parent-report measures of child psychosocial functioning^29^
Appropriate for children 0–17 years old, not limited to young children	
Utilises independent, direct, observational assessment of neurodevelopment, not solely reliant on parent-report	
Categorises impairment according to severity (typical, mild, moderate, severe), not dichotomous (e.g., the presence or absence of impairment)	

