##### Health service costs

Prospective cost of delivering *index and reference tests* to participating children will be surveyed from practitioners and include: (1) discipline of the practitioner administering the test; (2) mode of delivery (e.g., clinic, home, school or telehealth); (3) travel time and costs; (4) test administration time; and (5) indirect administration time for the assessment (e.g., scoring and interpretation).

Usual cost of *reference tests* will be collected from clinical managers in a structured interview, including time taken to administer and score each measure, travel time and other costs.

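### Phase I aims at primary-care use but neither secures nor names an accuracy estimate for RNDAs given by primary-care staff, so the overall figure may not carry over to them

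*Protocol article*

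**What the plan says.** **Intended use.** The abstract describes the study as one of "rapid assessments (index tests) that can be administered by a range of primary healthcare practitioners". The Introduction sets Phase I the aim of establishing accuracy for "index tests) that can be used to detect FASD in primary healthcare (Phase I"). Table 1 gives as a reason for choosing the RNDA: "Delivered by non-specialists trained to certification in administration, important for rural and remote sites lacking specialists". The Summary expects the findings to show how primary healthcare can support FASD assessment.

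**Who gives the tests.** The Phase I Procedure section lets trained Aboriginal Health Workers, nurses and midwives give the index tests, and also "allied health, General Practitioners (GPs) and/or paediatricians (when available"). If a site has nobody available for a test, "clinicians with relevant qualifications from the research team will administer the missing test". Separation of testers is conditional: "Where possible, index tests and reference tests will be administered by different practitioners". Five of the seven named sites are hospital services. No number or proportion of index tests given by primary-care staff is fixed.

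**What is analysed and recorded.** The Phase I part of Data analysis lists ROC curves, sensitivity, specificity, predictive values, likelihood ratios, kappa, correlations and Bland-Altman plots. It refers to the overall result and to domains, but names no breakdown by administrator. Under Health service costs in Phase II, the practitioner survey records the "discipline of the practitioner administering the test". Data analysis says that test results and survey data are matched to participants before de-identification.

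**The concern.** The RNDA is a structured observational assessment, with prompting and modelling by the person who gives it. Its accuracy may therefore depend on who that person is. The strengths-and-limitations box itself counts paediatricians and allied health as specialists, and both groups may give the index tests. Because separate testers are required only where possible, an allied health clinician experienced in FASD diagnosis could give both the index and the reference test to the same child.

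If such clinicians obtain more accurate RNDA results than nurses, midwives, Aboriginal Health Workers or GPs, the overall figure will flatter the test in the hands for which it is intended. The cost side is better served: Phase II compares primary healthcare with specialist services and plans interaction terms. Accuracy, the primary outcome, has no matching comparison in the article.

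**Working it through.** **Which results depend on the administrator (Table 3)**

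- RNDA only: motor, cognition, memory (3 domains).
- RNDA and BASC-3: language, attention, affect regulation, adaptive behaviour (4 domains).
- BASC-3 only: academic achievement, executive function (2 domains).

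The BASC-3 is completed by parents and teachers. Administrator type thus bears on 7 of 9 domains, most directly on the 3 that use the RNDA alone, and on the FASD call, which requires three severe domain concerns.

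**The plan's own precision (Sample size section)**

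Inputs: N = 200, 55% with FASD, sensitivity 80%, specificity 90%, alpha 0.05. This gives 0.55 × 200 = 110 children with FASD and 90 without. Half-width = 1.96 × √(p(1−p)/m).

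- Sensitivity: 1.96 × √(0.80 × 0.20/110) = 7.5 points.
- Specificity: 1.96 × √(0.90 × 0.10/90) = 6.2 points.

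Both stated figures are reproduced. They describe all 200 children together.

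**Precision for the primary-care subset**

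The article does not give the share of index tests done by primary-care staff, so the share is assumed and shown as a range. The other inputs are unchanged, and m is the expected number of children.

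| Share | With / without FASD | Sensitivity | Specificity |
|---|---|---|---|
| 100% | 110 / 90 | ±7.5 | ±6.2 |
| 75% | 82.5 / 67.5 | ±8.6 | ±7.2 |
| 50% | 55 / 45 | ±10.6 | ±8.8 |
| 25% | 27.5 / 22.5 | ±15.0 | ±12.4 |

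These use the plan's 80% sensitivity. If sensitivity in primary-care hands were 70%, the half-width at a 50% share would be 1.96 × √(0.70 × 0.30/55) = 12.1 points.

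**What an overall figure could hide (illustration with assumed values)**

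Let f be the primary-care share among children with FASD. Then overall = f × primary-care + (1 − f) × specialist, so primary-care = (overall − (1 − f) × specialist)/f. Take an overall sensitivity of 80%.

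- Specialist 85%: f = 0.50 gives (0.80 − 0.425)/0.50 = 75%; f = 0.25 gives (0.80 − 0.6375)/0.25 = 65%.
- Specialist 90%: f = 0.50 gives (0.80 − 0.45)/0.50 = 70%; f = 0.25 gives (0.80 − 0.675)/0.25 = 50%.

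The specialist values are not taken from the document. They show only that an overall 80% is compatible with quite different primary-care values.

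**The case against.** **The article is silent; it does not state that results are pooled.** A reader might infer that Phase I commits to a single pooled estimate. The text does not say so. A breakdown by tester could sit in the full protocol or analysis plan, which are not shown. That stands for the analysis. It does not remove the design point: the Procedure section mixes administrators and sets no minimum primary-care share, and an analysis plan cannot create primary-care tests that were never done.

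**The study can still answer the question.** A reader might go further and conclude that Phase I cannot show accuracy in primary-care hands. The documents do not support this. Discipline is recorded and survey data are matched to participants, so the split is feasible; its precision depends on an unknown share.

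**The primary outcomes do not restrict the administrator.** They compare index with reference tests, and the Summary is hedged. This is therefore a question of generalisability, not a contradiction. The abstract, the Introduction and Table 1 nevertheless make primary-care use the purpose.

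**The gap may be small.** RNDA training includes video review by a certified scorer, fidelity is checked quarterly, and inter-rater reliability is reported as sound to excellent. These lower the risk. The reliability statement does not name rater types, so it does not show that specialists and primary-care staff are interchangeable.

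**The research-team fallback may mainly concern reference tests.** The sentence refers to any missing test, so this is possible. The point does not depend on it. Some allied health staff may also work in primary care, so the grouping needs a definition.

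**Conclusion.** The point holds as a limit on what the overall accuracy figure can support. The plan aims at primary-care use, permits specialist administration without a floor, and in the article names no estimate for primary-care administrators. The consequence is confined to the RNDA-based domains and the composite FASD call; academic achievement and executive function are not affected.

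The size of any bias is unknown, because the documents give neither the primary-care share nor a difference in accuracy between administrators. What can be stated is the loss of precision: under the plan's own assumptions, from ±7.5/±6.2 points to about ±10.6/±8.8 at an assumed half share and ±15.0/±12.4 at an assumed quarter share.

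**What to change.** In the Phase I part of Data analysis:

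1. Keep the overall estimate.
2. Add sensitivity and specificity with 95% confidence intervals, for the FASD call and the RNDA-based domains, by type of RNDA administrator (primary-care staff versus paediatrician, allied health or research-team clinician). Use the discipline already collected for costing.
3. Assign allied health staff to a group in advance, according to the setting in which they work.
4. Report the number of children in each group, and base any statement about primary-care use on the primary-care-administered subset and its own interval.

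No new measurement is needed. There are two costs. The intervals are wider, as tabulated. Administrator type is also not randomised and may follow site, remoteness and case-mix, so a difference between groups could reflect those and not the tester. The split should therefore be descriptive, shown with site and case-mix, and not read as an effect of tester skill.

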#### Primary and secondary outcomes

The first primary outcome will determine the diagnostic accuracy of identifying FASD with index tests compared with reference tests. The second primary outcome will determine the accuracy of identifying impairment within each domain assessed. It is hypothesised that the rapid assessments (index tests) will have good sensitivity and specificity when identifying: (a) the presence of an FASD diagnosis (i.e., presence of three severe neurodevelopmental concerns plus prenatal alcohol exposure), and (b) impairment in each neurodevelopmental domain.

Comprehensive neurodevelopmental assessments can result in the accurate diagnosis of multiple neurodevelopmental disorders. Therefore, a secondary outcome will determine the accuracy of index tests in diagnosing other childhood neurodevelopmental disorders that co-occur, or occur independently of FASD, such as attention-deficit hyperactivity disorder (ADHD) and autism spectrum disorders (ASD).

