### Data analysis

#### Phase I: diagnostic accuracy

All data will be entered into an Research Electronic Data Capture (REDCap) database hosted by Griffith University.^19^ Data will be identifiable until all test results and survey data are matched to participants. Data will be de-identified for analysis. Prespecified test positivity cut-offs reflecting clinical norms (e.g., T score>70) will be used, receiver operating curves will also be used to explore best possible cut-offs. Standard diagnostic statistics will be calculated, including: receiver operating curves, sensitivity, specificity, positive and negative predictive values and likelihood ratios (using 95% confidence intervals).^20^ Kappa statistics will be used to compare the reliability of the classification of children as normal/moderately impaired versus severe on each measure of the neurodevelopmental domains.^21^ Continuous scores are available for many of the assessments, which will be used to calculate correlations between matched scores from the index tests and reference tests. Bland-Altman plots will examine the agreement between matched index test and reference test scores, overall and by domain.^21^ These plots will also help to determine if any difference between the index and the reference is influenced by the actual scores on the tests (e.g., if the index-standard difference is larger when children have low or high scores). Diagnostic outcomes from the index tests will be compared with diagnostic outcomes from the reference tests to explore whether the index tests function as an effective screening tool for FASD.

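### Blinding between index and reference tests is stated without condition, but one practitioner may give both, and nothing says the reference diagnosis is made blind to index results

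*Protocol article*

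**What the plan says.** All of the relevant rules on testing stand in the protocol article, Phase I, Procedure.

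- Separation of testers is conditional: "Where possible, index tests and reference tests will be administered by different practitioners".
- The next sentence is unconditional: "Practitioners administering index tests will not have access to reference test results, and vice versa, until all tests are scored".
- The two pools of testers overlap. The index-test list runs from Aboriginal Health Workers to paediatricians and includes allied health. On the other side, "Reference tests will be administered by allied health clinicians with relevant qualifications and credentialing for the tool".
- Where a site lacks staff for a test, of either kind, "clinicians with relevant qualifications from the research team will administer the missing test".

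The first primary outcome (Phase I, Primary and secondary outcomes) is accuracy for FASD, described as "presence of three severe neurodevelopmental concerns plus prenatal alcohol exposure". The second is impairment in each domain. A secondary outcome is accuracy for other disorders such as ADHD and ASD. The Data analysis section for Phase I says "Prespecified test positivity cut-offs reflecting clinical norms (e.g., T score>70) will be used", and "Diagnostic outcomes from the index tests will be compared with diagnostic outcomes from the reference tests". The article does not say who makes the reference diagnosis, when it is made, or what that person has seen.

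**The concern.** There are two separate gaps.

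**Same tester.** The conditional sentence allows one practitioner to give both sides to a child. That practitioner necessarily knows the first result when giving the second, so the unconditional sentence is untrue for that child. The article has no rule, record or analysis for this case. A subset of unknown size that was not blinded would enter both primary outcomes unmarked. The RNDA is an observational assessment in which prompts and modelling may be given (Measures), so knowledge of another result has room to act.

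**Diagnosis.** The blind is a rule for people who administer tests, and it lapses once everything is scored. The first primary outcome is a diagnosis, not a score. If the reference diagnosis is reached by clinical judgement after index results are open, those results could pull it toward agreement.

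In either case, movement toward agreement raises sensitivity and specificity together. The confidence interval does not show this and a larger sample does not remove it. The study is meant to support the use of rapid tests in diagnosis, so the error would favour that conclusion.

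**Working it through.** **1. The plan's own precision.** Inputs from Sample size: 200 children, 55% with FASD, sensitivity 80%, specificity 90%, alpha 0.05. Half-width = 1.96 × √(p(1−p)/n).

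- Sensitivity: n = 200 × 0.55 = 110; 1.96 × √(0.8 × 0.2/110) = 7.5 points, as stated.
- Specificity: n = 90; 1.96 × √(0.9 × 0.1/90) = 6.2 points, as stated.

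Nothing in this point changes those figures.

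**2. Where one tester could produce both results.** From Table 3, two of the nine domains (academic achievement, executive function) have only the BASC-3 as index, which is a parent and teacher report. Affect regulation has a previous diagnosis as its reference. The other six (9 − 2 − 1) pair an RNDA subscale, sometimes with the BASC-3, with a reference test given in the study. In the two BASC-3 domains the practitioner does not generate the index rating, but may still know it when giving the reference test.

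**3. When testers differ.** Access is closed in both directions until all tests are scored. Reference domain scores are therefore fixed before any index result is seen, and the domain-level outcome is protected.

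**4. Illustration of size, by assumption only.** Expected cells at the plan's figures: TP = 88, FN = 22, TN = 81, FP = 9. Let a share f of the reference classifications that disagree with the index move to agree with it. Then FN become TN and FP become TP:

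- Sensitivity = (88 + 9f)/(110 − 13f)
- Specificity = (81 + 22f)/(90 + 13f)

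| f | Sensitivity | Specificity |
|---|---|---|
| 0 | 80.0% | 90.0% |
| 5% | 80.9% | 90.6% |
| 10% | 81.8% | 91.1% |
| 15% | 89.35/108.05 = 82.7% | 84.30/91.95 = 91.7% |
| 20% | 83.6% | 92.2% |
| 30% | 85.5% | 93.3% |
| 50% | 92.5/103.5 = 89.4% | 92/96.5 = 95.3% |

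An f of 15% would arise, for example, if 30% of children were exposed and half of the discordant cases among them moved (0.30 × 0.50).

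**5. Against the planned precision.** Sensitivity rises by 7.5 points when 88 + 9f = 0.875 × (110 − 13f), that is f = 8.25/20.375 = 0.40. Specificity rises by 6.2 points when 81 + 22f = 0.962 × (90 + 13f), that is f = 5.58/9.494 = 0.59.

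**6. If the index result is the one that moves** (reference given first by the same tester), FN become TP and FP become TN. Sensitivity = (88 + 22f)/110 and specificity = (81 + 9f)/90. At f = 15% this gives 83.0% and 91.5%; at 50%, 90.0% and 95.0%. The order of testing hardly alters the picture.

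**The case against.** The strongest reply concerns the diagnosis. A reader might infer that results are released before the diagnosis is made, and so that index results shape the reference standard. The article does not say this. It gives no timing and names no decision maker. It describes FASD by a count of severe domains plus exposure, applies prespecified cut-offs, and has the research team extract test scores from records. All of this is compatible with a rule applied to scores already fixed under the blind, which later access could not move. A condensed article may also leave such detail to a fuller document. This part of the reply stands: the risk is conditional, not demonstrated.

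It does not close the gap. The text does not commit to a rule. The diagnosis also needs inputs that are not test scores, such as prenatal alcohol exposure and brain structure. Table 3 is a table of domain tests, and no score rule for ASD is evident from it.

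On the same-tester part, the overlap is limited. Nurses, midwives, health workers and doctors appear only on the index side. The reference battery is multidisciplinary, so one overlapping person would probably hold only part of it. That narrows the exposure but does not remove the contradiction, because allied health and research-team clinicians can still give either side.

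**Conclusion.** The point holds in two parts of different strength. The first is a contradiction in the text: the unconditional blinding sentence cannot be kept for a child tested by one practitioner, which the sentence before it permits, and such children are not marked. The second is a gap: the stated blind ends at scoring, and nothing says that the reference diagnosis is made without index results.

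The size cannot be determined from the documents. The figures above rest on an assumed share of discordant cases moving toward agreement. At 15% the effect is under 3 points on each measure, well inside the planned precision. A rise of about 9 points in sensitivity, larger than the planned ±7.5, needs half of all discordant cases to move; the ±7.5 is passed only at about 40%. A reader should not take the 9-point figure as an expected bias. Nor is domain-level accuracy at risk across the whole sample: it is exposed only where one person gave both tests.

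**What to change.** (a) In Procedure, move the end of the blind from completion of scoring to the moment when the reference domain ratings and the reference diagnosis have been recorded and locked. State that the reference diagnosis is made from reference-side information only: reference tests, prenatal alcohol exposure, brain structure and prior diagnoses, without index results. Limiting it to reference test scores would leave out the last three.

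(b) Record a same-practitioner flag for each domain in REDCap, and limit the blinding statement to children with different testers. Scoring and locking the first test before the second starts is not a substitute, because the tester still knows the first result when giving the second.

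(c) Report the number of flagged children, give accuracy with and without them, and describe the flagged ones as unblinded.

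The cost is some wording, a database lock and one flag per domain. Index results reach the team slightly later, and the analysis without flagged children is less precise because it uses fewer of them. No sample-size change follows. The flag should be recorded at testing, since affected children may not be reliably identifiable afterwards.
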